# Effects of passive blood-flow-restriction and electromyostimulation on ICU-acquired weakness (ICUAW): a study protocol for a randomized-controlled, parallel-group clinical trial

**DOI:** 10.1186/s13063-025-08874-y

**Published:** 2025-06-01

**Keywords:** ICU-acquired weakness (ICUAW), Blood flow restriction (BFR), Electromyostimulation (EStim), Critical illness rehabilitation, Muscle atrophy prevention, Intensive care unit (ICU) interventions, Passive physiotherapy, Ischemic preconditioning (IPC), Critical care muscle metabolism, Randomized controlled trial (RCT)

## Abstract

**Background:**

Intensive care unit-acquired weakness (ICUAW) is a prevalent secondary disorder in critically ill patients, characterized by significant loss of muscle mass and strength, often leading to prolonged ICU stays, increased mortality, and reduced post-discharge quality of life. Despite guidelines recommending early mobilization, logistical challenges and inconclusive efficacy have limited its impact on ICUAW prevalence. This study aims to assess the feasibility, safety, and clinical efficacy of exclusively passive physiotherapeutic interventions, including blood flow restriction/ischemic preconditioning (BFR/IPC) and electromyostimulation (EStim), as potential alternatives for muscle preservation in ICU patients who are often sedated or unable to participate in active rehabilitation.

**Methods:**

This prospective, randomized controlled trial will recruit 120 patients from the surgical ICU at the University Hospital Bonn, who meet the inclusion criteria of a > 48-h ICU stay. Patients will be randomized into four groups: Sham-Control, BFR/IPC, EStim, and combined BFR/IPC + EStim. The study’s primary endpoints include feasibility and safety metrics, such as patient compliance and stress response, alongside secondary endpoints related to clinical outcomes like ICU length of stay, ICUAW prevalence, muscle mass preservation, and rehabilitation efficacy. Measurements include non-invasive assessments of muscle mass, intramuscular microdialysis to monitor metabolic and inflammatory markers, and health-related quality of life evaluations post-discharge.

**Discussion:**

Preliminary literature and a systematic review underscore the need for resource-efficient, non-invasive interventions in ICU settings. BFR/IPC and EStim present promising results, but existing data on their efficacy in ICU populations are limited. This study’s findings will provide foundational data on the viability of passive physiotherapy techniques in ICU settings, potentially improving patient outcomes and reducing healthcare costs associated with prolonged ICU stays. If successful, these results will inform a multicenter randomized trial to further evaluate these interventions. This research represents a crucial step in developing feasible rehabilitation protocols to mitigate ICUAW, addressing a critical gap in critical care management and rehabilitation.

**Trial registration:**

ClinicalTrials.gov DRKS00033592. Registered on March 05, 2024.

## Introduction

### Background and rationale {6a}

Intensive care unit acquired skeletal muscle weakness (ICU-acquired weakness, ICUAW) is a secondary disorder while patients are being treated for life-threatening conditions [1]. This syndrome includes critical illness polyneuropathy and myopathic changes in muscle function with associated significant loss of muscle mass (−17% in 10 days) and strength, and can be considered as a serious and expensive complication that compromises rehabilitation and full recovery [2]. In systemic reviews, ICUAW has a prevalence of approx. 43% and primarily affects the proximal limb and respiratory muscles [1]. The pathophysiology of this secondary condition is mostly unknown. Previous findings suggest a decrease in anabolic effector hormones with reduced protein biosynthesis due to immobility, mitochondrial dysfunction, and upregulated atrophy signaling with impaired autophagy processes [3]. Mitochondrial biogenesis is impaired during severe illness/sepsis [4, 5], and alterations between the interaction of the mitochondrial marker TFAM and TFMB2 have been shown to impact on survival [6].

Patients suffering from progressive muscle wasting show a longer ICU stay, higher re-intubation, and higher mortality rates before and after hospital discharge [7]. While the rate of ICU-survivors is steadily increasing due to modern drugs and interventions, ICUAW is causing an even higher number of physically severely impaired patients after discharge from the hospital. Epidemiological data from ICU survivors show a readmission rate of over 50% and mortality of 30%, especially during the first year after discharge [8]. If patients survive the first year, they suffer from significantly reduced physical capacity and limitations in their quality of life [9]. Furthermore, in patients of working age, a return-to-work rate of approximately 49% one year after discharge from the hospital is evident [8]. While the costs of an ICU stay with long-term intubation (> 20 days) and subsequent rehabilitation in the USA are estimated to be at around 300,000 $ [10], the estimated European post-discharge period with costs of around 30,000 € in the first and 18,000 € in the second year represents a major financial burden for the patient and the healthcare system as well [11].

#### Practical problems and potential passive solutions

Current guidelines for intensive care therapy recommend early mobilization of patients to prevent ICUAW. In clinical practice, however, physiotherapy exercises for ICU patients are extremely complex, only manageable with a considerable number of staff, and can rarely be carried out to the full extent, especially in sedated and intubated patients. An increasing shortage of personnel resources reduces the possibility of daily physiotherapy services as well. However, meta-analyses show that even early mobilization, if feasible, is not associated with a lower ICUAW prevalence or shorter ICU length of stay [12, 13]. These results could be due to two different reasons: (1) the interventions carried out were not intensive enough to provide the necessary stimulus to counteract muscle atrophy or (2) physical therapy treatment is unsuitable in the critical illness phase, as this is perceived as additional stress for the body or muscle preservation is physiologically not possible in this phase.

Therefore, the primary objective of this study is to investigate the clinical feasibility and safety of exclusively passive physiotherapeutic interventions in critical illness. The applied interventions, which consist of purely metabolic (blood flow restriction/ischemic preconditioning, BFR/IPC training), mechanical (electromyostimulation, EStim), or combined metabolic/mechanical load (BFR/IPC + EStim), will additionally be examined for their effects on the course of intensive therapy, physical and mental health/compliance of patients, and clinical outcomes (e.g., length of intensive care stay, length of hospital stay, prevalence of ICUAW, rehabilitation). It is intended that the results of this study will serve as a basis for subsequent projects regarding muscle metabolism and exercise therapy in ICUAW in a multi-center approach.

#### Level of evidence: narrative review

In preparation for this scientific study, an extensive literature analysis was carried out using the PRISMA guidelines in the following databases through December 2023: PubMed and Cochrane. The search about the impact of ICUAW was conducted using the following three searching combinations, with the database-specific boolean operators, were entered in each data base: (1) “intensive care” AND “muscle atrophy” (2) “intensive care” AND “ICUAW,” (3) “intensive care unit” AND “muscle loss” (4) “intensive care” AND “blood flow restriction training” AND (5) “intensive care” AND “electrical muscle stimulation”. The literature search included all randomized and non‐randomized studies, as well as systemic reviews and meta-analysis with adult patients up to the 31.12.2023. Articles in English and German were applied. In addition, citations of previously published meta-analyses and relevant reviews were manually searched, and the reference lists were reviewed to identify additional pertinent studies. The results of the five searching combinations were:*PubMed*: combination 1: 12 hits; combination 2: 21 hits; combination 3: 7 hits; combination 4: 0 hits; combination 4: 7 hits.*Cochrane*: combination 1: 88 hits; combination 2: 84 hits; combination 3: 28 hits; combination 4: 1 hits; combination 4: 46 hits.

#### Discussion of evidence

ICUAW shows a prevalence around 48% (95% CI, 39%, 56%) and is associated with an average loss of muscle mass of around 2.1%/day (M. rectus femoris: 95% CI, − 3.17, − 1.02) (level of evidence, LoE [14]: 1 A, 3.251 patients; [15]). Among these, older patients with pre- or sarcopenic conditions are particularly vulnerable to ICUAW and show higher ICU mortality, which is related to substantial loss of muscle mass (LoE: 1 A, 3.249 patients; [16]). The diagnosis of ICUAW is determined by sonographic muscle measurement in 85% of the studies included in meta-analyses (LoE: 1 A; [17]). The development of ICUAW is associated with a prolonged duration of mechanical ventilation, longer ICU and hospital stays, and mortality (LoE: 1B, 415 patients; [18]) and has a negative impact on rehabilitation after hospital discharge. Meta-analyses report increasing healthcare-related costs, 1-year mortality, and when it comes to survival after the ICU period, reduced physical activity outcomes compared to control groups over several years after hospital discharge (LoE: 1 A, 1.755 patients; [19]). These data can also be confirmed by observations from our research group that showed significantly reduced health-related quality of life in all tested domains, including mobility, life activities, and self-care. This was examined, using the WHO Disability Assessment Scale 2.0, 1 year after ICU discharge in patients who survived a long-term ICU-stay (unpublished data, data available for reviewers upon reasonable request).

Because of the reduced recovery of ICU survivors, the search for interventions to counteract the development of ICUAW and its associated complications is intensifying. The “early mobilization” (EM) recommended in the S3 guideline of the German Society for Anesthesiology and Intensive Care Medicine e.V. (DGAI) “Lagerungstherapie und Mobilisation von kritisch Erkrankten auf Intensivstationen” shows only inconclusive results in the meta-analyses (LoE 1 A, 1.304 patients; [12]) without showing a positive effect on the rehabilitation of patients after discharge from the ICU. There is evidence of short-term effects on physical-related outcomes (LoE: 1 A, 709 patients, [20]) if physiotherapeutic exercise is started within the first 48–72 h of intensive care (LoE: 1 A, 1.726 patients, [21]). The insufficient outcomes are mainly attributed to the heterogeneity of the patient population, their reduced trainability (no possibility of active participation), and the limited feasibility in the hospital, as physiotherapeutic exercise of intensive care patients is associated with high costs and personnel resources.

Therefore, new intervention methods are needed that can provide sufficient training against the development of ICUAW, which are safe for patients and require few costs and human resources. Within this regard, electrical muscle stimulation (EStim) appears to be a safe intervention strategy which can associated with EM have positive impact on extubation success in ICU patients (LoE: 1 A, 1.312 patients, [22]). However, the quality of evidence for EStim to reduce ICUAW and improve rehabilitation after ICU discharge is low, mainly due to bias of the RCT trials and the heterogeneity of the enrolled population (LoE: 1 A, 140 patients; [23]).

The blood flow restriction (BFR) technique was only applied in one RCT so far (*n* = 20) and was able to show a reduction in muscle atrophy (*P* = 0.001) without indicating adverse effects (LoE 1B; [24]). However, this study shows methodological limitations compared to our planned study: The study was conducted with standard inflatable cuffs, which are not suitable for BFR training [25]. For this reason and to increase patient safety, a CE-certified surgical-grade tourniquet autoregulation device (personalized BFR, Delfi Medical Inc., Vancouver, Canada) is used in our study protocol for the BFR/IPC exercise. The present study is the first to investigate the connection between metabolic (BFR/IPC) and mechanical (EStim) load and its influence on intensive therapy. Furthermore, the effect of the exercise on the muscle is to be described directly and validly on the basis of intramuscular measurements by microdialysis.

### Objectives {7}

ICUAW is a prevalent and severe complication in ICU patients, leading to significant muscle loss, prolonged hospital stays, and increased mortality. Despite the recommendation for early mobilization, existing interventions often fail to prevent or mitigate ICUAW due to practical constraints and insufficient intensity. This feasibility study aims to explore passive physiotherapeutic interventions—blood flow restriction/ischemic preconditioning (BFR/IPC) training, and electromyostimulation (EStim)—as alternative approaches which can be applied to all ICU patients, including those who are sedated or intubated. These techniques could circumvent the challenges of active physiotherapy and address muscle atrophy without exacerbating the patient’s condition or requiring extensive resources. By evaluating the safety, practicality, and effectiveness of these methods, the study seeks to address critical gaps in current ICU rehabilitation practices, potentially improving patient outcomes and reducing healthcare costs.

The present project aims to investigate these two questions by examining the effect of a purely metabolic (blood flow restriction/ischemic preconditioning (BFR/IPC) training), mechanical (electromyostimulation, EStim) or combined metabolic/mechanical load (BFR/IPC + EStim) on the physiology of the critically ill patient and clinical outcome (e.g., ICU length of stay, duration of hospitalization, prevalence of ICUAW, rehabilitation).

For this project, endpoints were defined that primarily reflect the clinical feasibility and safety of the intervention methods and their combinability with the clinical objective of muscle maintenance during ICU therapy and hospitalization. The following domains of outcomes include the evaluation of the impact of the interventions on the clinical rehabilitation process and the description of the underlying mechanisms of possible positive or negative effects on skeletal muscle physiology using invasive diagnostic monitoring.

#### Clinical feasibility, safety and acute muscle condition

To assess the clinical feasibility and safety of the applied interventions and diagnostic techniques on patients’ mental and physical health, the following endpoints are investigated in this study:*Feasibility*: Questionnaires regarding patient compliance (e.g., acute measure of recovery and stress, AEB) and possible stress response to the interventions (e.g., VAS 0–100 mm).*Global Health & Safety*: Changes in drug application for supporting the cardiovascular system (e.g., noradrenaline), use of analgetic (e.g., fentanyl) and sedation drugs (e.g., propofol) and changes in respiratory gases before, during and after each intervention session. Daily assessment of inflammation and coagulation parameters.

Since ICUAW and the resulting complications in the process of rehabilitation can be attributed to compromised muscle health, specific outcome parameters were selected that allow an objective description of possible positive or negative effects of the course of therapy, applied interventions, and further hospitalization on skeletal muscle conditions. These parameters will be partially recorded daily or before and after the intervention period, as well as by discharge from the ICU and hospital:*Muscle Health*: Muscle mass and fiber angle, muscle strength, neuromuscular activation, body composition (by bioelectrical impedance analysis).

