#### Underlying mechanisms and physiological consequences by intensive care therapy and interventions

Given that the patient population included in this study can only be examined under certain conditions due to the state of sedation or mechanical ventilation, additional outcome parameters that can be collected independently of patient cooperation were selected. Furthermore, the selected endpoints make it possible to describe the internal load of the applied interventions, as well as to monitor the acute impact of the life-threatening disease and intensive therapy on changes in muscle metabolism and inflammation over the time of intervention:*Intramuscular measurements*: By implementing a microdialysis catheter (µDialysis, Stockholm, Sweden) into the *M. vastus lateralis*, which remains in the muscle for 8 days, it is possible to continuously measure metabolic impact (e.g., lactate, glucose, pyruvate) and inflammatory cytokines (e.g., IL-6, IL-8, IL-10, and TNF-α) of the ICU therapy and intervention on the muscle tissue. This minimally invasive technique enables the quantification of the acute influence of therapy on muscle tissue and to correlate it with changes in the other dimensions of the endpoints.*Systemic immune response*: For comparison between intramuscular immune responses to the disease, ICU therapy and the applied interventions, systemic immune response will be measured by analysis of inflammatory cytokines (TNFa, Interleukins) dependent on NFkB signaling [26] from the microdialysis samples and patient serum samples.

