
(3)In-exercise measurements
Physical and Mental Responses to Interventions:In order to analyze the impact of the interventions on patients mental and physical condition, before, each 10 min of exercise and after exercise, vital parameters such as blood pressure, pulse and oxygen saturation are measured. Furthermore, each from the beginning of the exercise intervention, each 10 min the applied medications for cardiovascular support, pain relief, and sedation are determined. For assessing the compliance of the patients to the interventions, subjective pain and exercise intensity will be obtained by visual analog scale (0–100 mm) and acute measure of recovery and stress (Akutmaß, Kurzskala, [32]).Blood Gas AnalysisBefore and after the exercise, a capillary blood sample is taken to visualize the venous blood gases (vBGA). The vBGA is used to determine carbon dioxide partial pressure (pCO_2_), oxygen partial pressure (pO_2_), oxygen content (ctO_2_), oxygen saturation (sO_2_), oxyhemoglobin fraction (FO_2_Hb), hemoglobin content (ctHb), oxygen half-saturation pressure (p50) and the concentration of lactate ([La^−^]), potassium ([K^+^]), sodium ([Na^+^]), calcium ([Ca^2+^]), bicarbonate ([HCO_3_^−^]), and chloride ([Cl^−^]).Intramuscular MonitoringDuring training interventions, the flow rate of the microdialysis catheter will be increased to 2 µl/min to get each 10 min a volume of 20 µl for analyzing the acute effects of the training interventions on muscle metabolism.

All outcome measures, there metric and timepoints are listed in Supplementary Table 2.

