### Recruitment {15}

The University Hospital Bonn has one of the largest surgical intensive care capacities in Germany (88 surgical intensive care beds). In the course of the feasibility study, all patients who meet the inclusion criteria can be enrolled in this study. To extend the inclusion to patients under sedation or mechanical ventilation, the consent to participate in the study by the “Ehegattennotvertretungsrecht” was also added and ethically confirmed. This allows the patient’s legal spouse, if they are not currently able to give consent, to be contacted and informed, and to confirm or decline participation in the study. During the pre-testing phase, a participation rate of 85% was achieved.

The feasibility of recruitment is derived from our experiences with the recruitment in previous intensive care projects. Approximately 3500 cases are treated at our institution’s surgical ICUs annually. Of these, approximately 5–10% have an extended stay < 7 days, making them good candidates for the proposed study. At the current rate of extended stay ICU patients, we expect to screen 25 patients per month. Of these we plan to recruit approximately 5–6 patients per month into the project, which means that in 36 months we can recruit up to 180 patients.

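### The feasibility part of the primary objective is measured by self-report that sedated patients cannot give and that does not record whether sessions were delivered

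*Protocol article*

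**What the plan says.** The Introduction (Practical problems and potential passive solutions) states that "the primary objective of this study is to investigate the clinical feasibility and safety of exclusively passive physiotherapeutic interventions in critical illness". The Abstract gives the same rank to the endpoints: "primary endpoints include feasibility and safety metrics, such as patient compliance and stress response".

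Objectives {7}, under Clinical feasibility, safety and acute muscle condition, has a separate Feasibility entry. Its content is "Questionnaires regarding patient compliance (e.g., acute measure of recovery and stress, AEB) and possible stress response to the interventions", with a 0–100 mm visual analogue scale (VAS) as the example for the stress response. Outcomes {12}, in-exercise measurements, repeats the idea: "For assessing the compliance of the patients to the interventions, subjective pain and exercise intensity will be obtained by visual analog scale", together with the short scale of acute recovery and stress.

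The intended population is wide. Objectives {7} describes interventions "which can be applied to all ICU patients, including those who are sedated or intubated". Eligibility {10} sets no requirement to be awake or able to communicate. Recruitment {15} explains the spousal consent route: "To extend the inclusion to patients under sedation or mechanical ventilation, the consent to participate in the study" was widened to the spouse.

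The article recognises the limit. Under Underlying mechanisms it says that these patients "can only be examined under certain conditions due to the state of sedation or mechanical ventilation", and it adds measures that need no cooperation. Those are intramuscular microdialysis and systemic immune markers, which serve the mechanistic aims and not feasibility.

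**The concern.** Two separate problems follow.

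The first is coverage. A subjective stress, pain or exertion score does not exist for a session in which the patient cannot communicate. The patients for whom a purely passive therapy is most relevant are then absent from the feasibility measure, and the result describes only sessions in which somebody could answer.

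The second is the construct. Even in a fully awake cohort, a pain or exertion score says how a session felt. It does not say whether the session took place, ran its full length, or was repeated on each of the 7 days. The Discussion promises to establish the feasibility of a 7-day course, and that is a question about delivery.

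At stake is the use of the results. The trial is meant to inform a multicentre trial, whose planners will need to know how much of the course can be delivered in this population.

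**Working it through.** **Is there a plan figure to reproduce?** None concerns feasibility. The only power figure is for muscle thickness: at least 75% per arm with 30 per arm, SD 2 mm and correlation above 0.9. Taking correlation 0.9 and assuming a two-sided familywise 5% level (not stated in the article):
- difference = 2.8 − 2.1 = 0.7 mm
- residual SD = 2 × √(1 − 0.9²) = 0.872 mm
- noncentrality = 0.7 / (0.872 × √(2/30)) = 3.11
- Dunnett critical value for three comparisons on 115 df = 2.378 (simulated)
- power = 76.7%

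The stated figure reproduces, but it has no bearing on feasibility.

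**The texts side by side**

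| Question | Where | Answer |
|---|---|---|
| Is feasibility primary? | Abstract; Introduction | Yes, with safety |
| What measures it? | Objectives {7}, Feasibility entry | Questionnaires and a VAS |
| What measures compliance? | Outcomes {12}, in-exercise | Pain and intensity VAS, short recovery and stress scale |
| Who is enrolled? | Objectives {7}, Eligibility {10}, Recruitment {15} | Sedated patients included by design |
| What needs no cooperation? | Objectives {7}, Outcomes {12} | Drug use, respiratory gases, vital signs, laboratory values, microdialysis, cytokines |
| Where do those sit? | Same sections | Global health and safety, physical responses, or mechanisms; not the Feasibility entry |

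No delivery-based measure is named as the feasibility endpoint.

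**How much information could be lost?** The article gives no share of patients unable to respond. As an assumption, let a fraction *a* be able to answer, from 25% to 75%, with 30 randomised per arm. The responders number n = 30*a*. The 95% half-width of a mean score per arm, in SD units, is t(0.975; n − 1)/√n:

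| *a* | n per arm | of 120 in total | half-width |
|---|---|---|---|
| 100% | 30 | 120 | 0.37 SD |
| 75% | 22.5 | 90 | 0.44 SD |
| 50% | 15 | 60 | 0.55 SD |
| 25% | 7.5 | 30 | 0.88 SD |

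This treats the ability to answer as fixed for each patient. Sessions are daily, so a patient who wakes during the week contributes later scores, and the real loss is by session. The table shows scale only, and it does not capture selection.

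**What delivery would offer.** Planned sessions per arm are 30 × 7 = 210, each observable whatever the patient's state. Sessions within a patient are correlated. With intraclass correlation ρ, the effective number is 210 / (1 + 6ρ), which runs from 210 at ρ = 0 to 210/7 = 30 at ρ = 1. Even at the worst limit every randomised patient counts.

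**The case against.** The strongest defence is that the lists are illustrative. The Abstract introduces its metrics as examples, the Feasibility entry does the same, and the full list of outcomes is in Supplementary Table 2, which is not shown. A delivery measure may stand there. This lowers certainty but does not remove the point. The examples given are kinds of questionnaire and stress scale, and the in-exercise text says directly that compliance is assessed by subjective scores.

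A second defence is that feasibility and safety are introduced jointly, and much of that joint list is objective. This stands for safety and for the physiological response to the sessions: medication and vital signs are recorded every 10 minutes. It does not tell us whether the 7-day course was completed.

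A reader might infer more than the documents support:
- *That the whole primary result describes an awake minority.* No share is given, and the safety data do not depend on wakefulness.
- *That intubated patients cannot answer.* Some are awake and may be able to mark a scale. The gap concerns patients unable to communicate.
- *That scores will be imputed for sedated patients.* Section {20c} imputes only if data are missing at random and does not mention these scores. What it lacks is a statement that a score is undefined in a period without communication.
- *That wakefulness will differ by arm and bias the comparison.* This is possible, since sedation follows randomisation, but nothing in the article shows that it will happen, and sedative use is itself recorded.

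**Conclusion.** The point holds for the feasibility component of the primary objective and for that component only. The measures named for it are unavailable whenever a patient cannot communicate, in a trial that recruits such patients by design. They also do not record delivery of the planned sessions. The safety component and the physiological measurements are not affected.

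The size of the loss is unknown. If between 25% and 75% of patients could answer, a mean score per arm would have a half-width of 0.88 down to 0.44 SD, against 0.37 SD with all 30; that range is an assumption. The construct problem depends on no such figure and would remain if every patient were awake. The conclusion rests on the article as published and would weaken if Supplementary Table 2 names session delivery as a feasibility endpoint. The change should be made before recruitment; the article gives the trial status as in preparation.

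**What to change.** In Objectives {7} and Outcomes {12}:

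1. Define the primary feasibility measure as the proportion of the 7 planned sessions per randomised patient that were delivered in full. Use all 7 planned sessions as the main denominator. Restricting it to days alive and in hospital would condition on events after randomisation.
2. Report missed or incomplete sessions by reason: death, discharge, or other. Give a version per eligible day as a supplementary result.
3. Report the proportion per arm with a 95% confidence interval that accounts for clustering of sessions within patients.
4. Keep the recovery and stress scale and the VAS scores as secondary tolerability outcomes, in sessions where the patient can respond. Report per arm how many could. State that scores are not imputed for periods when the patient could not respond.

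The cost is a change of definition and one extra log field per session. Staff are already present and recording every 10 minutes, so the added work is small. No change to the sample size or the interventions is needed.
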